## 9.2 Procedures by Visit

A schedule of the required study procedures and evaluations are outlined in Sections 9.1 and 9.2. Every effort should be made to complete the required procedures and evaluations at the designated visits and times (see Section 9.4 for allowable time tolerances).

### 9.2.1 Screening Period (Day -28 to Day -2)

Subjects will report to the study site for eligibility screening in between Day -28 and Day -2, inclusive. Before any study specific procedures are conducted, the subject must sign a written Informed Consent Form (ICF).

#### 9.2.1.1 Initial Screening Visit(s)

During this visit, the following study procedures will be administered to each subject:

- Informed consent
- SCID-5-CT
- Review of inclusion and exclusion criteria
- Subject demographics
- Review of medical and psychiatric history
- Review of prior medication history
- Height (cm)
- BMI
- Body weight (kg)
- Physical examination (including a neurological examination)
- Vital signs
- 12-Lead ECG
- Serology screen (for Hepatitis B surface antigen (HBsAg), serum antibody against Hepatitis C virus (anti-HCV antibody) and Human Immunodeficiency Virus (HIV))
- Urine cotinine screen
- Saliva alcohol screen
- Urine drug screen
- Serum pregnancy test (all female subjects)
- Clinical laboratory tests (hematology, biochemistry, and urinalysis)

- Ongoing AE surveillance
- Ongoing concomitant medication for AE inquiry & reporting

A mock MRI scan session can be arranged to acclimate subjects to the MRI scan environment and to rule out subjects who are claustrophobic or uncomfortable to stay inside the MRI scanner, if needed.

#### **9.2.1.2 Final Screening Visit (First Ketamine Session)**

Following the Initial Screening Visit(s), subjects who meet the initial enrollment criteria will report to the study site for a one-day Final Screening Visit.

During this visit, the following study procedures will be administered to each subject:

- Review of inclusion and exclusion criteria
- Review of prior medication history
- Body weight (kg)
  - Before behavioral assessments
- Physical examination (including a neurological examination)
  - Before behavioral assessments, Discharge
- Vital signs
  - Before behavioral assessments, Discharge
- 12-Lead ECG
  - Before behavioral assessments, Discharge
- C-SSRS – Baseline version
  - Before behavioral assessments
- Saliva alcohol screen
  - Before behavioral assessments
- Urine drug screen
  - Before behavioral assessments
- Urine pregnancy test (all female subjects)
  - Before behavioral assessments
- Ketamine infusion
  - 0 min

- MRI scan
  - 25 min prior to initiation of ketamine infusion: a 7-minute structural scan, a 2-minute phase map, and 2 sets of 30-second BOLD top-up scans
  - 15 min prior to initiation of ketamine infusion: 30-minute BOLD fMRI scan including pre-ketamine (15 minutes) and post-ketamine (15 minutes) scan
- Continuous ECG, pulse oximeter, blood pressure (BP) monitoring
  - throughout the MRI scan
- PK sample collection (ketamine)
  - 5 min post cessation of MRI scan
- BPRS
  - pre-ketamine: 2h prior to initiation of ketamine infusion
  - post-ketamine: immediately following the collection of PK sample for ketamine
- CADSS
  - pre-ketamine: 2h prior to initiation of ketamine infusion
  - post-ketamine: immediately following the collection of PK sample for ketamine
- PGx sample collection (optional)
- Ongoing AE surveillance
- Ongoing concomitant medication for AE inquiry & reporting

Subjects will be discharged following completion of safety procedures described above.

### **9.2.2 Treatment Period (Day -1 to Day 7)**

Following the Screening Period, subjects who meet the enrollment criteria will be admitted to the site on Day -1. Subjects will remain in the site during the Treatment Period. The following study procedures will be performed on Day -1 through Day 7.

#### **9.2.2.1 Day -1 (Admission)**

- Admission to site
- Review of inclusion and exclusion criteria
- Review of prior medication history
- Physical examination (including a neurological examination)
- Vital signs

- 12-Lead ECG
- C-SSRS – Since Last Visit version
- Saliva alcohol screen
- Urine drug screen
- Urine pregnancy test (all female subjects)
- Clinical laboratory tests (hematology, biochemistry, and urinalysis)
- Ongoing AE surveillance
- Ongoing concomitant medication for AE inquiry & reporting

#### **9.2.2.2 Day 1 to Day 5**

- Randomization (Day 1: prior to initial administration of investigational product)
- Vital signs (Day 3 only)
- 12-Lead ECG (Day 3 only)
- Administration of investigational product
- Ongoing AE surveillance
- Ongoing concomitant medication inquiry & reporting

#### **9.2.2.3 Day 6 (End of Treatment: Second Ketamine Session)**

- Body weight (kg)
  - Pre-infusion
- Physical examination (including a neurological examination)
  - Pre-infusion
- Vital signs
  - Pre-infusion
- 12-Lead ECG
  - Pre-infusion
- C-SSRS – Since Last Visit version
  - 3h post administration of investigational product
- Administration of investigational product
  - 0h

- PK sample collection (MGS0008)
  - 3h post administration of investigational product
- Ketamine infusion
  - 8h post administration of investigational product
- MRI scan
  - 7h 35 min post administration of investigational product: a 7-minute structural scan, a 2-minute phase map, and 2 sets of 30-second BOLD top-up scans
  - 7h 45 min post administration of investigational product: 30-minutes BOLD fMRI scan including pre-ketamine (15 minutes) and post-ketamine (15 minutes) scan
- Continuous ECG, pulse oximeter, BP monitoring
  - throughout the MRI scan
- PK sample collection (ketamine)
  - 5 min post cessation of MRI scan
- BPRS
  - pre-ketamine: 6h post administration of investigational product
  - post-ketamine: immediately following the collection of PK sample for ketamine
- CADSS
  - pre-ketamine: 6h post administration of investigational product
  - post-ketamine: immediately following the collection of PK sample for ketamine
- Ongoing AE surveillance
- Ongoing concomitant medication inquiry & reporting

#### **9.2.2.4 Day 7 (Discharge) / Early Termination (ET)**

Subjects will be discharged on Day 7 following completion of the procedures listed below:

- Physical examination (including a neurological examination)
- Vital signs
- 12-Lead ECG
- Clinical laboratory tests (hematology, biochemistry, and urinalysis)
- Ongoing AE surveillance

- Ongoing concomitant medication inquiry & reporting

Subjects who discontinue prematurely after receiving at least one dose of investigational product will complete the same Day 7 procedures before discharge.

### **9.2.3 Phone Call Follow-Up (Day 14)**

Subjects will be followed up by telephone by study staff on Day 14 to confirm general health and safety status, including any possible AEs. If the investigator deems follow-up safety assessments are required considering the AE, subjects will return to the study site for additional safety assessments.

### **9.2.4 Early Termination (ET) Phone Call Follow-Up**

Subjects who discontinue prematurely after receiving at least one dose of investigational product will be followed-up by telephone by study staff approximately 1 week after the date of last dose to confirm general health and safety status, including any possible AEs. If the investigator deems follow-up safety assessments are required considering the AE, subjects will return to the study site for additional safety assessments.

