## 6 STUDY DESIGN AND EVALUATION

### 6.1 Study Design

This study employs a randomized, single-blind, parallel-group design in healthy volunteers.

This study will enroll approximately 60 subjects. Following an up to 27-day outpatient Screening Period, eligible subjects will undergo an 8-day inpatient Treatment Period. Subjects will be randomized to one of three treatment groups in a ratio of 5:5:2 (25 subjects for a TS-134 20 mg group, 25 subjects for a TS-134 60 mg group and 10 subjects for a placebo group) (Figure 6-1). During the study, each subject will undergo a total of two ketamine sessions; a first session during a Screening Period and a second session on Day 6 of a Treatment Period. Each ketamine session will include one ketamine infusion with resting fMRI scanning from pre to post ketamine infusions. First and second ketamine sessions will be conducted at least 7 days apart. All randomized subjects will be dosed with TS-134 or placebo daily in a fed state, for 6 days during the study. TS-134 dose levels will be titrated according to the titration schedule shown in Table 6-1. Subjects' general health and safety status will be confirmed by a phone call one week following discharge from a Treatment Period.

[figure not shown]

Figure 6-1 Study Design

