### **Premature Discontinuation:**

Subjects may discontinue study participation at any time in this trial. All randomized subjects who prematurely discontinue participation after receiving at least one dose of investigational product will be followed-up by telephone by study staff approximately 1 week after their last dose administration (Early Termination (ET) Phone Call Follow-Up). Subjects who discontinue from the study prior to completion of the ketamine BOLD assessment on Day 6 may be replaced at the sponsor's discretion. See Section 8.4 for further details pertaining to early discontinuation procedures.

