8. History of recreational ketamine use, recreational PCP use, or an adverse reaction to ketamine. Subjects who have participated in prior research ketamine studies will be eligible providing they have participated in no more than 5 previous research ketamine infusions. Subjects can have infusions not more frequently than biweekly, and not more than 1/month on average, therefore subjects will need to wait 1 month if they had a single infusion and 6 weeks if they have had 2 closely spaced infusions prior to screening into the study.
9. Any subject who is unable to refrain from smoking throughout the study or with positive urine cotinine screen (> 400 ng/mL) at the Initial Screening Visit.
10. Any subject with a history and/or current evidence of serologic positive results for hepatitis B surface antigen, hepatitis C antibodies, or HIV antibodies 1 and 2 at the Initial Screening Visit.
11. History of violence, including any history of using a gun, knife, or other weapon with intent to harm someone, as well as a more than one physical fight without a weapon after the age of 18 years old (not including fights that happen during sports competition).

12. Presence or positive history of significant medical illness, including high blood pressure (SBP > 140 mmHg, DBP > 90 mmHg), low blood pressure (SBP < 100 mmHg, DBP < 60 mmHg), orthostatic hypotension (change in mean arterial pressure [ $1/3$  systolic +  $2/3$  diastolic] of > 20%) at Screening Visits (except for Final Screening Visit: Discharge) or Day -1 (Admission).
13. Any subjects who show subthreshold ketamine BOLD response (defined as % BOLD signal change of 0.5% at peak ketamine response) in ACC at Final Screening Visit.
14. Metal implants, pacemaker, other metal (e.g. shrapnel or surgical prostheses) or paramagnetic objects contained within the body which may present a risk to the subject or interfere with the MR scan, as determined in consultation with a neuroradiologist and according to the guidelines set forth in the following reference book commonly used by neuroradiologists: *Guide to MR procedures and metallic objects, F. G. Shellock, Lippincott Williams and Wilkins Philadelphia 2001*.
15. Claustrophobia.
16. Donation of one or more units of blood, plasma, or acute loss of an equivalent amount of blood within 60 days prior to Initial Screening Visit. (One unit= 450mL)

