### **8.1.6 Investigational Product Accountability**

The investigator is responsible for ensuring that all investigational products received at the site are inventoried and accounted for throughout the study. The dispensing of investigational product (TS-134 and placebo) must be documented on a drug accountability form which should include:

- Amount of dry bulk drug supplies received.
- Amount of dry bulk drug supplies currently stored.
- Label ID number or batch number.
- Amount of dry bulk drug supplies used for preparation of dosing solutions (for dosing and back-up)
- Dates and initials of person(s) responsible for each study medication inventory entry/movement.
- Amount of investigational product solutions prepared and amounts dispensed to each subject, including unique subject identifiers.
- Non-study disposition of dry bulk drug supplies and investigational drug solutions (e.g. lost, wasted, broken, unused back-up).
- Amount returned to sponsor or sponsor's authorized designee, or destroyed.

The investigator will retain and store all original containers until these containers are inventoried by the sponsor or sponsor's authorized designee.

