### **8.4 Discontinuation Criteria and Procedures**

In accordance with the Declaration of Helsinki, ICH GCP Guidelines, and the United States Food and Drug Administration (FDA) Regulations, a subject has the right to withdraw from the study at any time for any reason without prejudice to his/her future medical care by the physician or at the institution.

The investigator and sponsor also have the right to withdraw subjects from the study for reasons including the following:

- significant protocol violation on the part of the investigator or subject;
- unblinding of the subject, or designated unblinded investigator;
- significant noncompliance on the part of the subject;
- self-withdrawal, or refusal by the subject to continue treatment or observations;
- unacceptable toxicity;
- decision by the investigator that termination is in the subject's best medical interest and/or for safety reasons;
- unrelated medical illness or complication(s);
- sponsor decision to discontinue the study.

The sponsor may choose to terminate the study at any time for any reason. Should a subject decide to withdraw, all efforts will be made to complete and report the observations as

thoroughly as possible.

Should a subject discontinue prior to completion of the study, a final evaluation should be made at the time of the subject's withdrawal according to the procedures outlined in Sections 9.2.2.4 and 9.2.4. The reason for the withdrawal should be recorded and an Early Termination (ET) Phone Call Follow-Up evaluation approximately 1 week after the last dose of investigational product should be conducted. In the event that the subject cannot be contacted by phone, the site should make all necessary attempts to contact the subject to follow any adverse events.

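### In the visible text, subjects given ketamine at screening and then rejected under exclusion 13 have no scheduled contact after same-day discharge

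*Protocol*

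**What the plan says.** Section 9.2.1.2 puts the first ketamine session in a one-day outpatient visit. The dose is 0.23 mg/kg over 1 minute, at most 20 mg (section 9.3.5.1.1). Discharge follows a physical and neurological examination, vital signs and a 12-lead ECG.

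Section 7.2, item 13, then excludes "Any subjects who show subthreshold ketamine BOLD response" in the ACC at that visit. Only subjects who meet the enrollment criteria are admitted on Day -1 (section 9.2.2). Randomization and first dosing are on Day 1 (section 9.2.2.2).

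The later safety contacts are set out as follows.

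- Early-termination examination, section 9.2.2.4: "Subjects who discontinue prematurely after receiving at least one dose of investigational product will complete the same Day 7 procedures before discharge".
- Early-termination call, section 9.2.4: "Subjects who discontinue prematurely after receiving at least one dose of investigational product will be followed-up by telephone by study staff". Section 6.1 adds that the subject must be randomized: "All randomized subjects who prematurely discontinue participation after receiving at least one dose of investigational product will be followed-up by telephone".
- Day 14 call, section 9.2.3: "Subjects will be followed up by telephone by study staff on Day 14 to confirm general health and safety status". Section 6.1 says that subjects' "general health and safety status will be confirmed by a phone call one week following discharge from a Treatment Period".
- Section 8.4, for any discontinuation before the study is complete: a final evaluation under sections 9.2.2.4 and 9.2.4, and "Phone Call Follow-Up evaluation approximately 1 week after the last dose of investigational product should be conducted". If the subject cannot be reached by phone, the site is to keep trying in order to follow adverse events.

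Section 8.1.6 shows what the trigger term covers: "The dispensing of investigational product (TS-134 and placebo) must be documented on a drug accountability form". Ketamine is not included.

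**The concern.** Follow-up is tied to TS-134 or placebo, yet subjects receive ketamine before either. A subject rejected because of the response to that infusion has had a psychoactive drug and meets none of the conditions for a later contact. The ketamine risk text in section 12 says that ketamine can raise the risk of psychosis in healthy people too, and that exposure may predispose to later abuse. If such a reaction began after discharge in one of these subjects, the site would learn of it only if the subject called.

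What is at stake is the safety follow-up of screened volunteers. These subjects are never randomized, so no endpoint and no TS-134 comparison is affected.

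**Working it through.** The plan gives no figure to reproduce. The check takes each scheduled contact after the screening infusion and asks whether a subject rejected under exclusion 13 qualifies for it.

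| Contact | Condition in the protocol | Exclusion 13 failure qualifies? |
|---|---|---|
| Day -1 admission (9.2.2, 9.2.2.1) | Meets enrollment criteria | No |
| Day 7 / early-termination examination (9.2.2.4) | Enters the Treatment Period, or at least one dose of investigational product | No |
| Day 14 call (6.1, 9.2.3) | Discharged from the Treatment Period | No |
| Early-termination call (6.1, 9.2.4, Table 9-1 footnote e) | At least one dose of investigational product, timed from the last dose | No |

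The count of scheduled contacts after discharge is 0. A subject who completes the Day 6 ketamine session has 2: the Day 7 assessments and the Day 14 call.

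**What covers the screening visit itself.** The ketamine blood sample is due at 20 ± 5 min after ketamine (section 9.4), with the ratings immediately after it. The BPRS takes 20 to 30 min and the CADSS about 5 min (section 9.3.5.2). Assuming they are given back to back:

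- earliest end: 15 + 20 + 5 = 40 min after ketamine;
- latest end: 25 + 30 + 5 = 60 min after ketamine.

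The discharge examination has no stated clock time. The post-ketamine ratings ask about the experience during the scan, and the C-SSRS at this visit comes before ketamine. These checks can catch an acute reaction. They cannot catch one that starts after discharge.

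**Whether Day -1 can replace a call.** The calendar has no Day 0, because Day -1 to Day 7 is stated as 8 days. An infusion on Day -2 is therefore 1 day before Day -1. It is also 7 days before Day 6 (1 day to Day -1, 1 to Day 1, 5 to Day 6), so the rule of at least 7 days between sessions allows it. A Day -1 visit may thus come too early to stand in for a one-week call.

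**How many subjects.** The protocol does not say. For illustration only, let f be the share of infused subjects lost before dosing. Reaching 60 randomized then leaves 60 × f / (1 − f) such subjects:

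- f = 0.05: 60 × 0.05 / 0.95 = 3.2;
- f = 0.10: 60 × 0.10 / 0.90 = 6.7;
- f = 0.20: 60 × 0.20 / 0.80 = 15.0.

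The values of f are assumptions with no support in the protocol. They serve only to size the cost of the remedy.

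**The case against.** **Redaction.** The ketamine risk section is partly blacked out, and its visible end is the tail of a mitigation passage about monitoring during administration. A later contact could be described in the missing part, or in the separate safety plan that section 11.2.2 mentions. This stands as a limit: the finding is about the visible text. Neither Table 9-1 nor section 9.2, where a scheduled contact should appear, shows one.

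**Section 8.4.** A reader might infer that everyone who leaves before Day -1 is left without any provision. The text does not support that. Section 8.4 is not limited to dosed subjects, and it asks for a final evaluation and for continued attempts at contact. But it sends the site to two sections that are limited to dosed subjects, and it times the call from a dose that an undosed subject never had. For voluntary withdrawals the instruction is unclear. For an exclusion 13 failure, which is a failed entry criterion rather than one of the listed grounds for withdrawal, it sets no call.

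**The risk is small.** The same risk text says that the dissociative state is usually well tolerated and passes without treatment, and that no lasting harm from ketamine has been reported. Subjects with psychiatric disease, a first-degree relative with schizophrenia or psychotic mood disorder, recreational ketamine or PCP use, a prior adverse reaction to ketamine, or suicidal history are excluded. Scan monitoring is continuous, and the discharge examination covers psychiatric/behavior and mental status. All of this stands. Nothing suggests that subjects with a weak BOLD response are at higher risk.

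**Reporting rules already apply.** Adverse events and serious adverse events are reportable from consent, and known serious events are followed to resolution or stabilization. That is correct, but these are duties to report. They schedule no contact that would find an event.

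**Linking calls to the unapproved drug is coherent.** Ketamine is an FDA-approved anesthetic, and placebo subjects must be handled like TS-134 subjects. That explains the trigger. It remains odd that a subject who stops after one placebo dose is examined and called, while one who received only ketamine is neither examined again nor called.

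**Conclusion.** The point holds for subjects rejected under exclusion 13: 0 scheduled contacts after same-day discharge in the visible text. For voluntary withdrawals before dosing, the defect is an unclear instruction in section 8.4.

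Severity is minor. Three stronger readings are not supported.

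- That volunteers are left without safety oversight: the checks at the visit and the reporting rules are real.
- That subjects who go on to Day -1 may wait 27 days to be seen again: this would put the infusion on Day -28, the first screening day. The Final Screening Visit is a separate visit after Initial Screening, so the practical maximum is shorter.
- That a known number of subjects is affected: 3 to 15 follows only from the assumed losses of 5% to 20%.

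The conclusion assumes that the blacked-out ketamine text and the safety plan add no later contact.

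**What to change.** Amend sections 6.1, 8.4 and 9.2.4 and footnote e of Table 9-1. The existing follow-up call should also be made about 1 week after the screening ketamine infusion to any subject who received ketamine but is not dosed with investigational product. A Day -1 visit a week or more after the infusion can replace it. In section 8.4, time the call from the screening infusion when there was no dose; this also removes the ambiguity for voluntary withdrawals.

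The cost is protocol wording plus one phone call per affected subject, about 3 to 15 calls under the assumed losses. Staff already make such calls, and no visit or procedure is added. If the blacked-out text or the safety plan already provides such a contact, a cross-reference in section 9.2.4 is enough.
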